### Study population and eligibility criteria

All children suffering from SAM, without any complications, and aged 6–59 months, are eligible for inclusion in the present trial. Participants will be screened using weight-for-height/length *z*-score and mid-upper arm circumference (MUAC) as screening criteria. The criteria of the World Health Organization (WHO) will be used to diagnose edema among children. WHO defines children with grade 1–2 bilateral edema and a weight-for-height/length *z*-score of < − 3 standard deviations (SD) or MUAC of < 11.5 cm who are otherwise clinically healthy, aware, and with a decent appetite as children with SAM [28]. Trained healthcare staff including nurse, childcare worker, and doctor will assess the children for eligibility. MUAC will be assessed using WHO’s MUAC colored tapes in centimeters (cm), while weight-for-height/length *z*-score and weight of children will be assessed in grams (g) with minimal and light clothing using UNISCALE, and height will be measured using a standard measuring tape in cm(s) and then will be compared with the grading of *z*-score chart. All the anthropometric measures will be taken thrice to reduce information bias. Additionally, all the instruments that will be used for taking measurements will be checked for accuracy and zero precision beforehand. All eligible participants will be recruited following a pre-defined inclusion and exclusion criteria (Table 1).

**Table 1 Tab1:** Inclusion and exclusion criteria

*Inclusion criteria*	*Exclusion criteria*
Ages 6–59 months at enrolment	
Acute malnutrition without complications, as defined by the WHO (i.e., children with MUAC < 115 mm or weight-for-height *z*-score < − 3 or grade 1–2 bilateral edema who will be clinically well and alert with good appetite	Presence of any complications of severe malnutrition (severe dehydration, severe anemia, severe pitting edema, anorexia, hypothermia, high pyrexia, acute lower respiratory infection, or hypoglycemia) or immune compromised
Parental consent for the child to participate	Declined parental consent
Healthy children without any chronic or acute illness	Children on antibiotic treatment for any disease in the last 3 months

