### Sample size estimation

For sample size estimation, a balanced one-way analysis of variance power calculation with R software was used, and a minimum of sample of 53 participants was calculated for each group using 5% significance level, 80% power of study, 0.25 effect size (*f*) and 3 as *k* value (Fig. 2).

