**Fig. 2 Fig2:**
[figure not shown]
Sample calculation using R software

A calculated sample of 159 participants (53 participants each arm) is further inflated by 10% to account for attrition due to loss to follow-up, making a total sample of 174 participants with 58 participants required to be recruited in each arm. For achieving adequate participant enrolment to reach target sample size, community mobilization in the nearby areas of the selected hospitals through lady health workers will be carried out with the support of IRMNCH & Nutrition Program.

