### Randomization and allocation

Children suffering from acute malnutrition, otherwise healthy, aged 6–59 months, and fulfilling the inclusion criteria will be recruited randomly to one of the two arms of the present trial for 8 weeks, i.e., experimental and active comparator groups. However, healthy children with matched sex and age will be recruited from the vaccination centers of the research sites to the placebo comparator group as healthy controls. The participants in all groups will be recruited in equal allocation ratio (1:1:1) with no restriction of block size. A statistician unaware of the study method will generate the random numbers and allocate the participants to study groups by assigning unique code to them (i.e., SAM children to experimental and active comparator group and healthy children to placebo comparator group). All the participants will be given a recruitment card with their unique identity code mentioned on it.

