Furthermore, Statistical Package for Social Science (SPSS) version 24 will be used for evaluating the change in weight-to-height/length *z*-score, MUAC, neurodevelopment assessment, and muscle mass accumulation among trial participants. Firstly, for descriptive analysis, percentages and frequencies will be presented of qualitative variables (gender of the child, ethnicity, breast feeding history, and mother’s dietary habits), while mean ± SD (in case of normally distributed variables) and median ± inter-quartile range (IQR) (in case of skewed variables) will be given for quantitative variables. Furthermore, the association of the sociodemographic characteristics of the children and mothers with the weight-to-height/length z-score, MUAC, neurodevelopment assessment, and muscle mass accumulation among children will be explored through regression analysis. For comparing the outcomes between three trial groups, test of analysis of variance (ANOVA) will be used with Scheffe and Games-Howell test for post hoc multiple comparisons in case of normally distributed data; otherwise, Kruskal–Wallis test will be applied, while for analyzing the data of repeated measures within the same groups, paired-sample *t*-test (for normally distributed datasets) or will Wilcoxon test (for non-normally distributed datasets) will be applied. All the tests will be applied at 95% confidence interval (CI) by an independent statistician blinded to the study.

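### The between-group rule names two post hoc tests without saying which decides, and its rank branch yields no prebiotic-versus-starch contrast; a direct two-arm estimate would serve the randomised question better

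*Protocol article*

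**What the plan says.** Under Statistical analysis, the protocol article states one rule for comparing groups. It takes all three together in an ANOVA, and the follow-up and fallback are "Scheffe and Games-Howell test for post hoc multiple comparisons in case of normally distributed data; otherwise, Kruskal–Wallis test will be applied". The other tests in that sentence (paired t or Wilcoxon) are within-group and do not compare arms. No separate two-arm comparison is described.

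Under Randomization and allocation, children with SAM "will be recruited randomly to one of the two arms of the present trial for 8 weeks, i.e., experimental and active comparator groups". The third group is not part of that randomisation: "healthy children with matched sex and age will be recruited from the vaccination centers of the research sites to the placebo comparator group".

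Under Sample size estimation, the target of 53 per group comes from a power calculation for a three-group one-way ANOVA, whose other inputs are given as "using 5% significance level, 80% power of study, 0.25 effect size".

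The between-group sentence stands in the SPSS paragraph, which deals with change in weight-for-height z-score, MUAC, neurodevelopment and muscle mass. The diversity indices are described in the paragraphs before it, and the article does not say whether the same rule applies to them.

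**The concern.** Prebiotic plus RUTF against starch plus RUTF is the only randomised contrast, so it should have one defined estimate with one defined interval. The stated rule falls short of that in three ways.

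- **Two post hoc tests, no deciding rule.** Scheffe assumes a common variance; Games-Howell does not. They are joined by "and" under a normality condition, which says nothing about equality of variances.
- **Scheffe brings in the healthy children.** Its error term is the pooled within-group variance of all three groups, and at equal group sizes the healthy group carries one third of the weight. The width of the randomised comparison's interval then depends partly on spread in a non-randomised group.
- **The rank branch does not address the trial question.** Kruskal–Wallis tests whether any of the three groups differs. A small p-value could reflect only the difference between SAM and healthy children, and no pairwise contrast or effect estimate is named.

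At stake are the significance and precision reported for the randomised comparison, and, for outcomes judged non-normal, whether it is reported at all.

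**Working it through.** **The plan's own figure.** One-way ANOVA power with k = 3, f = 0.25 and alpha 0.05 has noncentrality k·n·f² and degrees of freedom 2 and 3(n − 1). It is 0.797 at n = 52 and 0.805 at n = 53, so 53 per group reproduces. Inflation: 53 × 1.10 = 58.3, taken as 58 per arm, 174 in total. The calculation concerns the omnibus three-group test.

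**Inputs.** n = 53 per group (from the article). r = healthy SD / SAM-arm SD is an assumption, since the article gives no SD; the range shown is 0.5 to 2. The true prebiotic-minus-starch difference of 0.55 SAM-arm SDs is also an assumption, chosen because the direct two-arm test then has about 80% power.

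**Critical multipliers for the pairwise difference**
- Two-arm t: t(0.975; 104) = 1.983
- Games-Howell: q(0.95; 3, 104)/√2 = 2.378
- Scheffe: √(2·F(0.95; 2, 156)) = 2.471

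Relative to the two-arm t, Games-Howell is 2.378/1.983 = 1.20 and Scheffe 2.471/1.983 = 1.25. Scheffe against Games-Howell is 2.471/2.378 = 1.04. At equal SDs, therefore, most of the extra width is multiplicity adjustment, which both tests carry.

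**Standard errors, in SAM-arm SD units.** The two-arm t and Games-Howell use √(2/53) = 0.194. Scheffe uses 0.194 × √((2 + r²)/3), a factor of 0.87, 1.00, 1.19 and 1.41 at r = 0.5, 1, 1.5 and 2.

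**95% half-widths (multiplier × standard error), power and disagreement.** Power and disagreement come from simulated normal data at a 0.55 SD difference.

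| r | Scheffe half-width | Games-Howell half-width | Two-arm t half-width | Scheffe power | Games-Howell power | Two-arm t power | Post hoc tests disagree |
|---|---|---|---|---|---|---|---|
| 0.5 | 0.42 | 0.46 | 0.39 | 75% | 67% | 80% | 8% |
| 1 | 0.48 | 0.46 | 0.39 | 64% | 67% | 80% | 4% |
| 1.5 | 0.57 | 0.46 | 0.39 | 46% | 67% | 80% | 22% |
| 2 | 0.68 | 0.46 | 0.39 | 26% | 67% | 80% | 41% |

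With no true difference between the arms, the pairwise rejection rate is about 2% for Games-Howell at every r. For Scheffe it is 3.4%, 1.4%, 0.4% and 0.07% at the same four ratios. Scheffe's behaviour on the randomised contrast thus moves with the healthy group's spread; Games-Howell's does not.

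**Rank branch.** No arithmetic applies. The text names an omnibus test and stops, so followed literally it produces one three-group p-value and no contrast or interval.

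**The case against.** Naming one equal-variance and one unequal-variance post hoc test is commonly read to mean that Scheffe applies if variances are equal and Games-Howell if they are not. That selection rule, and pairwise tests after Kruskal–Wallis, could sit in an analysis plan that is not shown. Games-Howell already uses the two-arm standard error, and at equal SDs the two tests differ by only 4% in width. Below r = 1 Scheffe has more power than Games-Howell, not less.

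All of this is fair and limits the point. It does not remove it, because the article does more than stay silent: it fixes the tests and makes normality the trigger. A variance pre-test would still let the healthy group's spread choose the error term for the randomised comparison.

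Three stronger readings are tempting and are not supported:

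- **That the healthy children's variance sets the error bar.** It has one third of the weight in Scheffe's pooled term and does not enter the Games-Howell standard error at all; there the third group affects only the multiplier.
- **That SAM selection must make the healthy SD larger.** The eligibility section says "Participants will be screened using weight-for-height/length" z-score and MUAC. Those criteria apply at baseline, are open-ended and are alternatives to one another, whereas the plan analyses change. Healthy children might well vary less in change than children recovering on RUTF.
- **That the healthy group by itself will push well-behaved data into the rank branch.** That would require normality to be judged on pooled data, and the article does not say how it is judged.

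**Conclusion.** The point holds in a limited form. As written, the rule does not say which of two tests with different variance assumptions decides the randomised comparison, and for non-normal outcomes it stops at a test that does not isolate that comparison.

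The size depends on an SD ratio that the article does not give. If the SDs are similar, the two post hoc tests nearly agree, and their cost against a direct two-arm test is mostly multiplicity adjustment (power 64% and 67% against 80%). If the healthy group is markedly more variable, Scheffe's power falls to between 46% and 26%, and the two tests give different answers in roughly a fifth to two fifths of trials. If it is less variable, Scheffe is the more powerful of the two. These figures assume normal data, 53 analysed per group and a 0.55 SD difference.

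A reader might also infer that the primary diversity analysis is compromised. The article does not tie this sentence to the diversity indices, so the point reaches them only if the same rule is meant to apply.

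**What to change.** For each outcome analysed under this rule, and for alpha diversity if the rule is meant to cover it, replace the ANOVA/Kruskal–Wallis switch for the randomised question with:

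- **Main comparison:** the prebiotic-minus-starch difference with a 95% CI whose standard error comes from the two SAM arms only (Welch or heteroscedasticity-robust).
- **Sensitivity analysis for skewed outcomes:** a two-arm rank or permutation test.
- **SAM versus healthy:** reported separately and labelled descriptive, using Games-Howell only.

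The cost is one paragraph of analysis wording, with standard methods and no extra data. The small downside is that the randomised contrast is no longer adjusted for the comparisons with the healthy group; the text should say so and give the reason, namely that those comparisons are not randomised and answer a different question.

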### Interim and additional analyses

No interim or temporary analysis has been planned for the present trial, as there are no anticipated harms of the interventions of the present trial.

### Quality control

For ensuring the quality of the data and trial, the trial steering committee, an Independent Data Monitoring Committee (IDMC) comprises a group of experts who are external to the clinical trial, and all the staff administered in the trial will be responsible. The administered trial staff responsible for randomization, allocation, data collection, and treatment administration will be provided with an extensive 2-day training by the principal investigator (first and second authors) before the initiation of the trial for introducing them to the specifics of the trial. Safety monitoring will be the responsibility of the Institutional Review Board (IRB) of University of the Punjab, who can inspect the records, documents, and assessors of the trial for ensuring the guiding principles of trial protocol with regular evaluation of data every alternate week during the trial. The IRB is independent of the study and does not have any competing interests. The trial steering group and the IDMC will conduct regular meetings every fortnight to review the conduct throughout the trial period for auditing.

### Patient and public involvement

No patient and public were involved during the design of the present trial.

### Protocol amendments

Any changes to the protocol will be updated in the clinical trial registry. Afterwards, the principal investigator will notify the trial centers and a copy of the revised protocol will be added to the investigator site file. Any deviations from the protocol will be fully documented using a breach report form.

### Dissemination

The results of the study will be published in a scientific journal, preferably open access, to reach the scientific community. In addition, the results will be communicated to the hospitals which are part of the study and, thereby, the health professionals working in these hospitals. There are no publication restrictions so that also the broader public will be addressed via postings in media.

### Trial status

Protocol version: 1.3 of December 4, 2023.

Recruitment start (expected): June 15, 2024.

Recruitment finish (expected): July 31, 2024.

### Trial registration

The present trial is registered at ClinicalTrials.gov with identifier No: NCT06155474. Registration date is December 4, 2023.

## Discussion

Children suffering from SAM are usually treated with RUTF; however, literature indicates that the iron content present in RUTF may not be sufficient to elevate the iron levels to the optimal range among them [21]. Considering this and the presence of symptoms of diarrhea, pneumonia, acute gastroenteritis, and acute respiratory infections among SAM children, the present trial aims to evaluate the effect of RUTF plus prebiotics on the management and gut microbiome diversity of SAM children. Malnutrition alters the gut microbiome of the children with the gut microbiota of SAM children less diverse as compared to the healthy ones [30]. However, literature highlights the role of prebiotics in stimulating the growth of specific taxa in the gut of the host conferring benefits to their health [31].

Previous studies clearly demonstrate the difference in the diversity of gut microbiome of healthy and malnourished children. Studies indicate a higher relative abundance of Bacteroides in the gut microbiome of children who suffer from diarrhea as compared to those who have recovered from it [32]. Further, the dominance of firmicutes has also been reported in the gut of the healthy host [33]. This is because children who encounter diarrhea at an early age might get impairment in the composition of their gut microbiota, resulting in continuous diarrhea, persistent illness, and underdevelopment [34], whereas GOS, as form of prebiotics, is proven to have positive effects on the growth of beneficial bacteria (including bifidobacterial in the gut), stool consistency, bowel function and transit time, support of natural defenses, and mineral absorption [35, 36]. This indicates that GOS could also provide beneficial results for treating the malnutrition among children by altering their gut microbiome. Likewise, previous trials reveal the beneficial effects of prebiotics on the health of SAM children [22, 37]. However, there is rarely any study that evaluates the role of prebiotics on the gut microbiome of SAM children, to the best of our knowledge.

The present trial is designed in a way that addresses this gap, reduces any potential biases, and pinpoints some major aspects of malnutrition among children that were lacked in the previous trials. However, there are some limitations that should be highlighted. First, the present trial is designed to be conducted in a single district, i.e., Lahore, and may not incorporate regional disparities. Secondly, the present study will evaluate the role of different treatment modalities on the gut microbiome of the children at the end of the trial and does not consider the relapse rate due to time and financial constraints, as the present study is not supported by any external funding sources. Furthermore, the data related to maternal characteristics will be recorded on verbal history which could potentially result in recall or observation bias. However, in order to overcome this, we are currently working to standardize the trial’s procedure and may also take maternal stool samples for analyzing the role of maternal gut microbiome on the child’s health.

## Conclusions

Conclusively, the results of the present trial are expected to indicate RUTF plus prebiotic as a cost-effective therapy for improving the gut microbiome diversity of SAM children and as a more effective therapy for treating SAM children as compared to RUTF individually. GOS present in prebiotics is proven to have positive effects on growth of bifidobacterial, stool consistency, bowel function and transit time, support of natural defenses, and mineral absorption that could also provide beneficial results for treating the malnutrition among children. This is the first trial that evaluates the effect of prebiotics on the gut microbiome diversity of SAM children, as per our knowledge. Despite of its limitations, the results of the present trial would provide useful insights and high-quality data for the treatment and management of SAM children by evaluating the effect of RUTF plus prebiotic on the gut microbiome diversity of children, leading to medical evidence for designing large-scale studies.

## Data Availability

The datasets analyzed during the current study and statistical code are available from the corresponding author on reasonable request, as is the full protocol.

## Abbreviations

CI: Confidence interval
DHQ: District Health Quarter
GOS: Galactooligosaccharides
IDMC: Independent Data Monitoring Committee
IQR: Inter-quartile range
IRB: Institutional Review Board
IRMNCH: Integrated Reproductive Maternal Newborn, Child Health
ITT: Intention-to-treat
MDAT: Malawi Development Assessment Tool
MUAC: Mid-upper-arm circumference
OUT: Operational taxonomic unit
RDP: Ribosomal Database Project
RUTF: Ready-to-use therapeutic food
S: Svedberg
SAM: Severe acute malnutrition
SD: Standard deviation
SPSS: Statistical Package for Social Science
WHO: World Health Organization
